## Abstract

**Background**: Influenza poses a substantial health burden, especially among older adults in China. While vaccination is one of the most effective preventions, influenza vaccine uptake rates among Chinese older adults remain low. This study examines the individual and combined effects of behavioral interventions based on the Information–Motivation–Behavioral Skills (IMB) model and economic incentives in promoting influenza vaccine uptake among older adults living in China. **Methods**: The study will recruit 640 older adults living in eight communities that have not been covered by the free influenza vaccination policy. These eight communities (as clusters), stratified by urban and rural, will be randomized to four parallel arms, including a usual care arm, an IMB-based behavioral intervention arm, a conditional economic incentive arm, and a combined behavioral-economic arm. The interventions will start from the beginning of the flu season and last for about one month. Specifically, the IMB-based behavioral intervention encompasses health education brochures, healthcare provider-led lectures, interactive quizzes, and personalized consultations. The exact number of economic incentives is conditional on the timing of vaccination (a higher amount for early immunization) and the number of people within a household to be vaccinated at the same appointment (a higher amount for more people). The primary outcome is the influenza vaccination rate. Data will be gathered through vaccination records and questionnaires covering IMB-based vaccination cognitions. Mixed-effects models will be used to analyze the outcome of vaccination rate, reporting difference-in-differences estimates with 95% confidence intervals. **Conclusions**: The results of this study have the potential to inform influenza vaccination program scaleup among older adults who are not yet covered by the free influenza vaccination policy. **Ethics and dissemination**: Ethics approval has been granted by the ethics commission of Peking University Health Science Centre (IRB00001052-24090). Participants will be required to sign a written consent form. Findings will be reported in conferences and peer-reviewed publications in accordance with the recommendations of the Consolidated Standards of Reporting Trials. **Registration number**: This study was registered at the Chinese Clinical Trial Registry (ChiCTR2400090229).

## 1. Introduction

Influenza annually impacts a substantial fraction of the world’s population, causing significant health, social, and economic consequences. Globally, influenza causes an estimated 3 to 5 million cases of severe illness and 290,000 to 650,000 respiratory deaths annually [1]. Older people are generally more vulnerable to influenza. Research indicates that over 85% of influenza-related deaths occur among individuals aged 65 and above [2]. In mainland China, studies have estimated influenza-associated all-cause mortality rates of 14.33 per 100,000 persons for all ages and 122.79 per 100,000 persons for those aged ≥ 65 years [2]. This is accompanied by a significant economic burden among older people infected with influenza [3]. Research indicates that the average hospitalization cost for older adults due to influenza—around CNY 14,000–19,000 (approx. USD 1929–2618)—is double that of non-older adults, equating to roughly 60% of the average annual income of urban older adults and twice that of rural older adults [4].

Vaccination is the most cost-effective means of combating influenza [5]. Studies have shown that the influenza vaccine, aimed at protecting high-risk groups from severe influenza cases, effectively reduced hospitalizations for pneumonia or influenza by 27–60% and lowered the mortality rate by 48–80% in community-dwelling older adults [6,7,8]. The WHO recommendations underscore the necessity of annual vaccination for older adults aged 65 and above, urging/calling upon its Member States to achieve at least 75% vaccination coverage among older adults by 2010 [9]. In most regions of China, the influenza vaccine is not part of the national broad immunization program, and individuals must pay the market price (about USD 20) to get the vaccination. Despite the significant geographical variations, the overall rate of influenza vaccination of older adults remains low across the country, ranging from 33% to 46% in regions offering free vaccination and 0.5% to 5% in regions without free vaccination [10].

Different levels of factors were found to be associated with influenza vaccination, including socio-demographics (age, education, occupation, health insurance coverage, income, living status, impaired functional status), health service-related factors (vaccination costs, recommendation from a physician, accessibility to healthcare services) and cognitive factors (vaccination awareness, low vaccine literacy, concerns about the vaccine’s side effects) [11,12,13,14,15].

To address these factors, various behavioral interventions aimed at increasing influenza vaccinations have been documented internationally and locally in China. Strategies to improve vaccination rates among older people have focused on enhancing access to vaccinations, addressing concerns about costs and side effects, and boosting awareness within communities [16]. Specific interventions have included sending reminders about the benefits of vaccination [17], providing health education messages [18,19], conducting home visits [19], and utilizing pharmacy-based vaccination delivery [20]. These approaches specifically target the barriers identified, such as limited access and lack of awareness, while also leveraging positive influences, such as community demand and healthcare provider recommendations.

Evidence suggests that interventions grounded in a theoretical framework tend to be more likely to succeed in increasing influenza vaccination rates [21]; theoretical frameworks commonly reported include the Health Belief Model (HBM), the Theory of Reasoned Action (TRA), and the Health Action Process Approach (HAPA) [22]. Among these, the Information–Motivation–Behavioral Skills (IMB) theory has been particularly influential in guiding the design of interventions to explain vaccine uptake behavior. The IMB theory posits that information, motivation, and behavioral skills are critical in influencing health behaviors. Information refers to an individual’s understanding of the vaccine, its benefits, and the risks associated with influenza. Motivation encompasses personal attitudes towards vaccination and social influences like norms and peer support. Finally, behavioral skills involve the practical abilities required to obtain the vaccine, such as accessing healthcare services and overcoming logistical barriers [23]. Research has shown that the low influenza vaccine uptake rates among Chinese older adults are highly related to low information, low motivation, and low behavioral skills [12,24], indicating that the IMB model has great potential to guide interventions to improve this vaccine uptake rate. Relevant constructs tested in previous interventions included vaccine knowledge, risk perception, beliefs about the vaccination benefits, subjective norms related to vaccination, and cues to action [12]. Additionally, existing studies that utilized the IMB framework have found that most of its elements were significantly associated with vaccine uptake intention and behavior [25].

Despite the popularity of theory-based interventions, the effectiveness of the interventions above had been mixed [16], and cross-study comparison was difficult because interventions varied depending on the setting and participants’ backgrounds. Third, behavioral interventions conducted in the Chinese setting are relatively limited, and very few studies have taken the urban-rural differences into consideration.

In addition to behavioral interventions, economic incentive-based interventions have emerged as another useful approach to bolster influenza vaccination rates [23]. Prior research underscores that economic incentives promoting health-conducive behaviors can stimulate behavioral shifts [25,26]. A pragmatic randomized controlled trial in Beijing, China, investigated the impact of financial incentives ranging from CNY 0 to 60 on influenza vaccine uptake among older adults (≥60 years). The findings showed that providing economic incentives boosted influenza vaccine uptake (41% with an amount of CNY 60 vs 37% without incentives) [27], and similar results have been observed in studies conducted in Singapore [28]. Incentives can boost vaccine uptake by lowering access barriers and enhancing motivation. They may include financial rewards or community recognition, which help offset costs and encourage individuals to seek vaccination. A quasi-experimental pragmatic trial evaluated the effectiveness of a pay-it-forward intervention in increasing influenza vaccine uptake among older adults in China, and the results were promising, with 60% in the pay-it-forward arm and 20% in the usual care arm [29]. The pay-it-forward intervention encouraged vaccinated individuals to support others in their community, creating a cycle of reciprocity. For instance, those who are vaccinated might contribute to a fund to help others get vaccinated. This approach not only increases individual uptake but also fosters community solidarity around health [29].

All of the economic interventions above were unconditional, meaning the participants received the incentive regardless of their vaccination behaviors. Conditional incentive and unconditional incentive may produce different outcomes in terms of intervention effect and cost-effectiveness [30]. A conditional incentive means that participants are given different choices, and they may receive different amounts of incentives based on the participant’s performance. Research indicates that community engagement and neighborhood social cohesion are important targets for promoting health behaviors among older adults [31,32]. These findings suggest that conditional economic incentive approaches that leverage social norms and family support can be a promising strategy for boosting vaccination rates among older adults.

Despite existing research on factors influencing older adults’ willingness to receive influenza vaccines and behavioral interventions, several knowledge gaps remain. First, influenza vaccine intervention programs often lack a solid theoretical foundation in health behavior, resulting in suboptimal intervention effects. Second, considering the prevalent practice of self-paid influenza vaccination in most parts of China, there is a pressing need for rigorous research to comprehensively evaluate the impact of economic incentive interventions on vaccination willingness and uptake, particularly in the Chinese setting, as the national program does not cover influenza vaccination.

The present study aims to test the effectiveness of IMB-based behavioral intervention and conditional economic incentives in increasing influenza vaccination among older adults in China through a randomized controlled trial.

## 2. Materials and Methods

### 2.1. Study Design

This study will use a cluster randomized controlled trial design, with the community as the unit of randomization and various interventions, to evaluate the effectiveness of IMB-based behavioral intervention and conditional economic incentives among the Chinese older adults. The primary outcome is influenza vaccination over the follow-up durations.

We will choose communities from different provinces where the influenza vaccine is not covered by the present health system and older adults needs to pay out of pocket. In the two targeted provinces (Jiangsu and Shandong), four communities will be selected from urban and rural areas within each province, resulting in eight communities in total. These eight communities will be stratified based on their urban or rural status and then randomly allocated to (1) the IMB-based behavioral intervention group, (2) the conditional economic incentives group, (3) the combined IMB-based behavioral intervention and conditional economic incentives group, and (4) the control group. We will assess influenza vaccine uptake before and after the intervention and between different study arms. Figure 1 illustrates the study design.

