### 2.4. Intervention

The intervention started before the influenza season, running from October this year to February next year. Before the start of the influenza season, the eight communities were randomly allocated into four study arms: (1) IMB-based behavioral intervention, (2) conditional economic incentives, (3) a combination of IMB-based behavioral intervention and conditional economic incentives, and (4) the control group with usual care, with stratification by urban and rural areas.

**IMB-based behavioral intervention.** The older adults will receive behavioral intervention based on the IMB model (Figure 2). The underlying idea of the intervention is that vaccination behavior is closely related to the older adults’ vaccine knowledge, their motivation to reduce the risk of influenza infection through vaccination, and vaccination-related behavioral skills. The IMB model includes the following components: (a) information, comprising objective and subjective vaccine information; (b) motivation, including perceived susceptibility, attitudes (towards vaccines), and complying with social norms (e.g., peer recognition of vaccine); and (c) behavioral skills, mainly encompassing vaccine-related self-efficacy (e.g., managing side effects), action planning (scheduling vaccinations), and coping planning (dealing with vaccination obstacles) [33]. The conditional economic incentives could lead to behavior change via potential pathways, involving modulating the price effect, enhancing the income effect, and mitigating high discounting or present bias [34].

The main components of the intervention, designed based on the IMB model, will be implemented offline and include the following:

(a) Distribution of health education brochures. The printed health education brochures summarizing official information on influenza vaccination from WHO and China’s National Health Commission will be distributed once after the baseline.

(b) Lectures on influenza vaccination. Influenza vaccination experts will lead the lectures. Topics will cover information about influenza vaccine, improving intentions for influenza vaccination uptake, social norms for vaccination, self-efficacy in vaccination and managing potential side effects, and creating effective action plans for vaccine appointments. The research team will provide lecture materials. This component will also take place once.

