### 2.7. Data Analysis

The mean and standard deviation will be used to describe the data for numerical variables such as intention to be vaccinated and scores on each element of the IMB model. The *t*-test will be used to compare the balance of baseline data between the intervention group and the control group for these variables. For categorical variables such as influenza vaccination, the rate will be used to describe the data, and the chi-square test will be used to compare the balance of baseline data between the intervention group and the control group.

We will estimate the Difference in Differences (DIDs) (with a 95% confidence interval (CI)) of the proportion of vaccine uptake between each intervention and control (non-intervention) arm, adjusting for the clustering effect and testing whether it is statistically significant or not at a 5% level of significance. This study will use mixed-effects models to evaluate the impact of the primary and secondary outcome indicators. A generalized mixed linear model will be used to assess the impact of categorical outcome variables, and a mixed linear model will be used to evaluate the effect of continuous outcome variables. The effect evaluation process will follow the intention-to-treat principle. All statistical analyses will be performed using IBM SPSS Statistics (version 27) and SAS (University Edition, version 9.4). The statistical significance level will be *p* < 0.05.

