Several practical and operational issues should be addressed to ensure the trial’s effectiveness and feasibility. First, to ensure a reasonable response rate and follow-up rate, we will provide participants with clear, easy-to-understand informational materials and ensure that follow-up procedures are streamlined and that participants receive reminders via multiple channels. Second, to ensure the study’s quality, we will provide standard training to all staff involved in participant recruitment and filing work. Third, to establish an objective measure of our primary outcome of vaccination status, we will obtain official vaccination records that will be provided and certified by the local health authorities (instead of self-reported data from our participants). Last, quality control measures will be instituted throughout the whole study process to monitor adherence to protocols and ensure consistency in data collection.

This study has several potential limitations. Firstly, its generalizability may be limited due to its focus on self-paid influenza vaccination within specific communities in China. However, existing research suggests that even in regions with free influenza vaccination, uptake rates remain low [42]. The behavioral interventions and economic incentives explored in this study hold promise for enhancing vaccine acceptance and uptake. Secondly, the effectiveness of economic incentives could be influenced by external factors, such as changes in the financial environment or variations in individual preferences for monetary rewards. To mitigate this bias, we consider affordability as a moderating variable in vaccine uptake. Additionally, given the varying influenza vaccination promotion policies across different regions, the study is subject to overestimating or underestimating the intervention effects. Lastly, it is important to note that the study duration might not fully capture the long-term sustainability of the observed effects. Future research could explore the adaptability of the IMB model and economic incentives in different cultural and economic contexts to provide more generalizable findings.

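### Community randomisation is stratified by urban/rural only, so under the natural layout there is a 5/6 chance that at least two arms are each confined to a single province, in a trial that names regional policy as a source of bias

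*Protocol article*

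**What the plan says.** All references are to the protocol article.

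- **Source of the communities (Section 2.1):** "In the two targeted provinces (Jiangsu and Shandong), four communities will be selected from urban and rural areas within each province, resulting in eight communities". The urban/rural split within each province is not given.
- **Unit of allocation (Section 2.1):** the trial is randomised "with the community as the unit of randomization".
- **Stratification:** Section 2.1 states that "These eight communities will be stratified based on their urban or rural status and then randomly allocated to" the four arms. Section 2.4 repeats that the draw is made "with stratification by urban and rural areas", and the Abstract agrees. Province is not named as a stratification factor or constraint in any of the three places.
- **Timing:** Section 2.1 puts the allocation in the future, while Section 2.4 says that "the eight communities were randomly allocated into four study arms" before the season.
- **Analysis (Section 2.7):** difference-in-differences of uptake, each intervention arm against control, with adjustment for clustering. For the model, "A generalized mixed linear model will be used to assess the impact of categorical outcome variables". No list of fixed effects is given.
- **Acknowledged bias (Section 3):** "given the varying influenza vaccination promotion policies across different regions, the study is subject to overestimating or underestimating the intervention effects". No design or analysis step is tied to this.

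**The concern.** With two communities per arm, the allocation decides whether an arm represents both provinces or only one. Urban/rural stratification balances the arms on that factor and leaves province to chance.

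This matters because the primary analysis compares each arm's change in uptake with the change in control. Any fixed difference between the provinces drops out of that comparison. A change that affects one province in the study season, such as a local promotion drive, does not. If an intervention arm lies wholly in one province and control wholly in the other, the whole of that change is added to or taken from the estimated effect. The article itself expects regional promotion policy to act in this way.

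An allocation rule differs from a modelling detail in one respect: an analysis plan written later can only partly repair it.

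**Working it through.** **Layout, reproduced from Section 2.3.** 576 / 0.90 = 640 participants; 8 communities x 80 = 640; 640 / 4 arms = 160 per arm; 160 / 80 = 2 communities per arm. Stratification makes these one urban and one rural. The article gives no probability of provincial imbalance, so there is no stated figure to compare with.

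**Assumption.** Two urban and two rural communities in each province (2+2). The alternative that still allows one urban and one rural community per arm is 1+3 in one province and 3+1 in the other.

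**Counting the draws (2+2).** There are 4! x 4! = 576 allocations. For province, only two choices matter: which two arms receive Jiangsu's urban communities, C(4,2) = 6 ways, and which two receive its rural communities, 6 ways. That gives 36 equally likely patterns of 16 allocations each.

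| Relation of the two pairs of arms | Single-province arms | Patterns | Allocations | Probability |
|---|---|---|---|---|
| Complementary | 0 | 6 | 96 | 1/6 |
| One arm in common | 2 (one per province) | 24 | 384 | 2/3 |
| Identical | 4 (two per province) | 6 | 96 | 1/6 |

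- P(at least two arms each confined to one province) = 1 - 1/6 = 5/6 = 83%.
- P(control confined to one province) = (2/3)(2/4) + (1/6)(1) = 1/2.
- Single-province arms occur equally often in each province. So whenever control is single-province, at least one intervention arm lies wholly in the other province: P(at least one opposite-province contrast) = 1/2.
- For a given intervention arm, P(wholly opposite to control) = (2/3)(2/12) + (1/6)(2/3) = 1/9 + 1/9 = 2/9. With probability a further 4/9, one of the two arms is mixed and the other is not.

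**Alternative split (1+3 / 3+1).** Exactly two single-province arms in 432 of 576 allocations (75%) and none in 144. A given contrast is opposite-province with probability 1/8. Control is single-province with probability 3/8, which is again the chance of at least one opposite-province contrast.

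**Size of the bias.** Let d be the difference between provinces in the season's change in uptake, in percentage points. Without a province term, the contrast is shifted by d when the arms lie in opposite provinces, by d/2 when one arm is mixed, and by 0 when both have the same mix. The planned difference in Section 2.3 is 16% - 8% = 8 points, so each point of d takes up one eighth of it in an opposite-province contrast. The documents give no value for d.

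**What adjustment can recover (2+2).** Take community-level changes with common variance s², and additive terms for arm, stratum and province.

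- *Two single-province arms.* Province is estimated only from the two mixed arms, as half the difference between their urban-minus-rural gaps: variance (2s² + 2s²)/4 = s². The unadjusted opposite-province contrast has variance s²/2 + s²/2 = s². Adjusted, it has 2s², so the standard error rises by √2 = 1.41.
- *Degrees of freedom.* 8 communities - 4 arms = 4; with stratum 3; with province as well 2. The t quantiles are 3.18 on 3 df and 4.30 on 2 df. At equal residual variance the interval is 1.41 x 4.30 / 3.18 = 1.9 times as wide.
- *Four single-province arms.* Province is then a function of arm, and opposite-province contrasts cannot be separated from it. This happens in 6 of 36 patterns (1/6). For a given contrast the probability is (1/6)(2/3) = 4/36. It cannot occur under the 1+3 / 3+1 split.
- *No single-province arm.* An additive province effect cancels from every arm contrast without any adjustment.

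**The case against.** Several points can fairly be made for the plan.

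- **Adjustment is usually possible.** A reader might infer that arm and province can never be separated once an arm is confined to one province. The layout does not support that. With additive terms every contrast stays estimable in 30 of 36 patterns. What stands is that the estimate is then imprecise, depends on additivity, and fails for some contrasts in the other 6.
- **Difference-in-differences already protects.** It does so for stable differences between provinces, but not for changes particular to the season.
- **The model may be completed elsewhere.** Section 2.7 lists no fixed effects at all, and an analysis plan not shown may include stratum and province. So their absence from the article is not an error in itself. A reader might also infer a marked loss of precision from leaving out the stratum. The documents do not support a figure: they give no urban-rural gap, and a stable gap would cancel.
- **The 83% can be misread.** It does not mean that two or more arms share the same province and lie wholly in it; that probability is 1/6 under 2+2 and zero under the alternative split.
- **The limitation is disclosed, and in terms of regions rather than provinces.** True, but disclosure does not balance the arms, and the two provinces are the largest regional division in the design.
- **The draw may be over, and Figure 1 is not shown.** If the allocation made was balanced by province, stating so settles the main point. If not, the actual arm-by-province table matters more than the prior probability.

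**Conclusion.** The point holds as a weakness of the stated allocation rule. The three places that describe stratification name urban/rural alone, for eight communities drawn from two provinces. Under the 2+2 assumption the chance that at least two arms are each confined to one province is 5/6 (75% under 1+3 / 3+1). The chance that at least one intervention-control contrast lies wholly across provinces is 1/2 (3/8 under the alternative).

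The harm depends on a province-specific change in the study season. The article considers regional policy effects plausible but does not quantify them, so the bias cannot be sized beyond the d and d/2 rule above. The firm part is the randomisation. The modelling part is a request for clarity, because the covariates may be set out in a document not shown.

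**What to change.** **If allocation is still open:** restrict the draw so that each arm receives one community from each province as well as one urban and one rural. Under 2+2, 96 of the 576 allocations qualify (6 patterns x 16). Draw one of these at random. Single-province arms then have probability 0, urban/rural balance is kept, and no participants are added. Full stratification by province and urban/rural together is not feasible, since each cell would hold two communities for four arms.

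**If allocation is done:**

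1. Report the arm-by-province table, with urban/rural shown.
2. Flag any intervention-control contrast whose arms lie in opposite provinces, and say whether it can be adjusted.
3. Include the urban/rural stratification factor in the primary model.
4. Give a province-adjusted sensitivity analysis, stating that it assumes additivity.

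The cost is one table and 1 to 2 between-community degrees of freedom: from 4 to 3 with the stratum, and to 2 when province is added. In either case, reconcile the tenses of Sections 2.1 and 2.4 so that the status of the draw is clear, and state the urban/rural split within each province.
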